## Abstract

**Background:**

Treatment of patients with multimorbidity is challenging. A rational reduction of long-term drugs can lead to decreased mortality, less acute hospital treatment, and a reduction of costs. Simplification of drug treatment schemes is also related to higher levels of patient satisfaction and adherence. The POLITE-RCT trial will test the effectiveness of an intervention aiming at reducing the number of prescribed long-term drugs among multimorbid and chronically ill patients. The intervention focuses on the interface between primary and secondary health care and includes a pharmacist-based, patient-centered medication review prior to the patient’s discharge from hospital.

**Methods:**

The POLITE-RCT trial is a cluster randomized controlled trial. Two major secondary health care providers of Mecklenburg-Western Pomerania, Germany, take part in the study. Clusters are wards of both medical centers. All wards where patients with chronic diseases and multimorbidity are regularly treated will be included. Patients aged 65+ years who take five or more prescribed long-term drugs and who are likely to spend at least 5 days in the participating hospitals will be recruited and included consecutively. Cluster-randomization takes place after a six-month baseline data collection period. Patients of the control group receive care as usual. The independent two main primary outcomes are (1) health-related quality of life (EQ-5D) and (2) the difference in the number of prescribed long-term pharmaceutical agents between intervention and control group. The secondary outcomes are appropriateness of prescribed medication (PRISCUS list, Beers Criteria, MAI), patient satisfaction (TSQM), patient empowerment (PEF-FB-9), patient autonomy (IADL), falls, re-hospitalization, and death. The points of measurement are at admission to (T0) and discharge from hospital (T1) as well as 6 and 12 months after discharge from the hospital (T2 and T3). In 42 wards, 1,626 patients will be recruited.

**Discussion:**

In case of positive evaluation, the proposed study will provide evidence for a sustainable reduction of polypharmacy by enhancing patient-centeredness and patient autonomy.

**Trial registration:**

Current Controlled Trials ISRCTN42003273

## Background

Along with demographic and epidemiologic changes, *polypharmacy* becomes a pressing challenge. More and more people suffer from chronic diseases and multimorbidity [1-3] and are treated with an increasing number of drugs. Whereas polypharmacy usually refers to the intake of five or more long-term drugs at the same time [4,5], patients with multiple chronic diseases are often treated with ten or more drugs [6-8]. In Germany, the prevalence of polypharmacy among elderly patients is about 27% and doubles to 54% when including over-the-counter medications (OTC) [9].

Treatment of patients with multimorbidity is challenging; medical guidelines tend to focus on a solitary chronic disease. In patients with several chronic diseases conflicting recommendations are likely to occur. Polypharmacy, thus, involves severe risks for patient safety; it is associated with a reduced ability to perform tasks of daily living, with an increased risk for impaired cognitive capacity, and with rising incidence of geriatric syndromes, such as delirium, falls, and urinary incontinence. In addition, patients with polypharmacy witness an increased rate of adverse drug events and drug interactions [10-12]. Among geriatric patients, 10%–15% of all hospital admissions are related to adverse drug events [13]. Adverse drug events increase both morbidity and mortality [12-15]. Previous research shows that a reasonable reduction of long-term drugs can lead to decreased mortality, less acute hospital treatment, and a reduction of costs. Simplification of drug treatment schemes is also related to higher levels of patient satisfaction and adherence [5,14,16-20].

In the past, different tools have been developed to assess and optimize medication in chronically ill patients. In 1991, Beers et al. presented a first catalogue of criteria to detect inappropriate substances among older people—the Beers Criteria for Potentially Inappropriate Medication Use in Older Adults [20,21]. Due to different “markets” and prescribing behavior, countries such as Canada, France, and Germany created their own lists of potentially inappropriate medication (PIM). In 2010, the first German PIM list was published; the PRISCUS list is based on international literature and specific characteristics of Germany. It is systematically consented by experts in the field [22,23].

Furthermore, the usage of OTCs is rising steadily. Very often, though, patients do not perceive OTCs as medication. Although nearly 30% of German adults periodically make use of herbal preparations—primarily as dietary supplements—they rarely report the usage to their doctors [24,25]. Among patients with multimorbidity, who are using a high number of drugs, these dietary supplements can cause severe drug interactions such as bleeding [26] or reduced plasma drug levels [27].

Interventions relying on a concept where pharmacists provide information to clinicians have shown effects on reducing inappropriate prescriptions [12]. Standardized prescription-feedback [28] and educational outreach visits also showed to have some effect towards the reduction of inappropriate multiple medication [12,16,17]. Studies have been conducted in different settings, however, focusing mainly on nursing homes or secondary care. Despite promising results [11,14,29,30], there is still a lack of robust evidence on the sustainability of the effects of medication reviews [31]. Whereas some trials lacked a control group [9,12], others failed to reduce polypharmacy in the long run [5,32,33]. As far as the latter are concerned, patients’ and primary care physicians’ preferences to switch back to the previous medication scheme have been identified as a major problem [34-37]. In sum, there is evidence for the efficacy of well-planned and performed interventions to reduce polypharmacy. However, evidence for effectiveness and efficiency is still lacking, especially as far as effects on patients’ quality of life are concerned [38].

### Objectives

The POLITE-RCT trial will test the effectiveness of an intervention aiming at reducing the number of prescribed long-term drugs among multimorbid and chronically ill patients aged 65+ years. The intervention focuses on the interface between primary and secondary health care and includes a pharmacist-based, patient-centered medication review prior to the patient’s discharge from hospital. This approach is innovative and particularly promising, as hospitalization of older, multimorbid and chronically ill patients is often related to an increase in the number of prescribed long-term drugs [39,40]. It will be the first trial to systematically assess the effectiveness of the described intervention which is based on both *evidence and patient preferences*. The POLITE-RCT trial is built on previous research; the POLITE pilot study proved that the intervention is feasible. Reactions of patients, pharmacists, ward physicians, and general practitioners (GPs) were positive. On average, the number of prescribed long-term pharmaceutical agents was reduced by one per patient [8,41].

## Methods

### Trial design

The POLITE-RCT trial is a cluster randomized controlled trial. Two major secondary health care providers of Mecklenburg-Western Pomerania, Germany, will take part in the study. Together, both centers with a total of four hospitals treat about 80,000 patients a year in urban and rural settings. The study will, thus, be conducted in a setting that represents the real health service situation.

### Clusters

Clusters are wards of both medical centers including medical personnel and patients cared for during the observational periods. A ward is defined as an entity with stable medical personnel. In case of responsibility of senior physicians for two or more wards, these wards will be randomized together.

#### Inclusion criteria

All wards of the participating centers where elderly patients with chronic diseases and multimorbidity are regularly treated will be included. These are, e.g., units of internal medicine, geriatrics, abdominal and vascular surgery, orthopedic surgery, and neurology.

#### Exclusion criteria

Wards currently participating in other trials or projects aiming at optimizing drug therapy will be excluded.

### Participants

#### Inclusion criteria

Patients aged 65+ years who take five or more prescribed long-term drugs that are systemically acting (topic administration excluded) and who are likely to spend at least 5 days in the participating hospitals will be recruited and included consecutively.

#### Exclusion criteria

Patients who are not able to take their medication by themselves, who are not able to give legal informed consent (e.g., due to dementia), patients with severe language difficulties, and those who suffer from deafness as well as patients taking part in another clinical trial will be excluded. Further, patients with the following diseases that usually make polypharmacotherapy unavoidable are excluded: active malignoma, acquired immunodeficiencies (HIV), and hemodialysis. Also, post-transplant patients as well as patients having a remaining life expectancy of less than 12 months will be excluded.

### Recruitment

Each week, up to 30 eligible patients will be recruited per hospital consecutively at admission. Pharmacists will inform about the study and will seek written informed consent. Recruitment will be stopped as soon as the necessary number of patients per week is reached.

### Randomization

Cluster randomization takes place after a 6-month baseline data collection period. During this period, no intervention will be performed. This allows collecting information about potential confounders and cluster imbalances. Based on that, the decision for or against stratified randomization will be made. Computer-assisted randomization will be performed by a statistician not involved in patient recruitment, data collection, and data management.

### Intervention

During in-patient treatment of patients affected by polypharmacy, a pharmacist specially trained in communication skills performs a *narrative-based medication review*. Thus, two approaches are combined here: the face-to-face clinical “brown bag” medication review [42] and the patient-centered approach of narrative medicine [43,44]. Apart from detecting potentially inadequate medication, a major aim is to identify patient preferences and to include them—whenever possible—into a hierarchically structured list of evidence-based medication recommendations. Thus, priorities for medication modification can be based on both “objective” pharmaceutical considerations as well as on “subjective” patient preferences. The pilot study showed that this approach motivated patients to actively contribute to the reduction of medication. The *narrative-based medication review* itself takes approximately 30–45 min. The pharmacist then prepares a list of possible drugs to be stopped. Pharmacists have access to a clinical decision support system [45]. The list will be discussed with the hospital physician in charge and will be submitted for adjustment with the patient’s individual GP. The active involvement of the patient’s GP aims at bringing transparency into the decision-making and might increase chances for a sustainable optimization of medication by preventing relapse to old medication patterns (as frequently observed in other studies). See Figure 1.

**Figure 1 Fig1:**

**The intervention cascade.**

### Control group

Patients attending wards randomized into the control group will not receive a medication review but receive care as usual. Medication data will be obtained from patient records. Contamination between control and intervention group will be minimized by careful and strict separation of functional units.

### Outcomes

#### Primary outcomes

The independent two main outcomes are (1) health-related quality of life (EQ-5D) [46-48] and (2) the difference in the number of prescribed long-term pharmaceutical agents between intervention and control group at T3. Since in Germany, combination drugs are frequently used, the primary outcome focuses on pharmaceutical agents rather than on number of drugs.

#### Secondary outcomes

The secondary outcomes are appropriateness of prescribed medication (PRISCUS list [22], Beers Criteria [49,50], MAI [51,52]), patient satisfaction (TSQM) [53,54], patient empowerment (PEF-FB-9) [55], patient autonomy (IADL) [56], falls (frequency and severity) [57], re-hospitalization, and death. For all patients ensured with the largest public German health insurance provider AOK, cost-effectiveness will be analyzed by the Scientific Institute of the AOK (WIdO). In addition, data on socio-demographic characteristics [58] will be collected. See Table 1.

**Table 1 Tab1:** **Overview of instruments and time of measurements**

**Outcome**	**Instrument**	**Time of measurement**			
		**T0**	**T1**	**T2**	**T3**
**Primary outcomes**					
Health-related quality of life	EQ-5D	X		X	X
Difference in the number of prescribed long-term pharmaceutical agents	Number of prescribed long-term pharmaceutical agents	X	X	X	X
**Secondary outcomes**					
Appropriateness of prescribed medication	PRISCUS list, Beers Criteria	X	X	X	X
	Medication appropriateness index (MAI)	X	X	X	X
Patient satisfaction	TSQM	X		X	X
Patient empowerment	9-item shared decision-making questionnaire (PEF-FB-9)	X		X	X
Patient autonomy	Instrumental activities of daily living scale (IADL)	X		X	X
Falls	*Frequency*: number of falls in the previous 6 months	X	X	X	X
	For each fall, *severity* will be assessed:				
	*Moderate*: bruising, sprains, cuts, abrasions, or reduction in physical function for at least three days or if participant sought medical help				
	*Severe*: fractures, admission to hospital with an injury, or if stitches were required				
Re-hospitalization				X	X
Death			X	X	X
Cost-effectiveness	Difference in health care costs between both groups				X

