#### Points of measurement

Prior to the intervention, baseline data will be collected. During the following intervention period, for each patient of the intervention and control group, primary outcomes will be measured at four points in time: at admission to (T0) and discharge from hospital (T1) as well as 6 and 12 months after discharge from the hospital (T2 and T3).

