### Statistical methods

The unit of inference will be the individual. Then, analyses will be carried out at cluster and at individual level. In a first simple approach, data in each cluster will be collapsed to construct a relevant summary measure (mean with standard deviation). This essentially removes the need to adjust for clustering effects. Of course, for variable-sized clusters, this analysis does neither take into account the intra-cluster correlation nor the cluster sizes and is less efficient than an individual-level analysis. But nevertheless, the relative simplicity of a cluster-level analysis still remains an advantage, albeit with some loss of efficiency and an inability to adjust for individual-level risk factors. In a second step, generalized estimating equations (GEE) models will be applied [60,61]. A generalized linear model takes into account within-group correlation and allows adjustment for the joint effects of cluster-level as well as individual-level factors without the requirement of parametric assumptions.

A model that takes into account the randomized clusters (wards) as random effect, with EQ-5D change or difference in prescribed long-term pharmaceutical agents between intervention and control at T3 as dependent and random group as independent variables, will be fitted to the data. In this model, baseline (T0) values of primary variables and a selection of further baseline characteristics of ward or patient will function as covariates. The intervention effects are quantified by the between-group differences of the corresponding estimates of changes from baseline from the fully adjusted model, which we assume to give the best account of the study results. In the statistical analyses, missing values will not be replaced. Methods for dealing with outliers will be defined in the statistical analysis plan (SAP) or in an addendum to the SAP. Secondary efficacy variables will be analyzed in an explorative way. Similarly, confidence intervals computed will be interpreted as interval estimates for presence or absence of effects in the study data. Intention-to-treat analyses will be performed.

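### The six-month recall for falls at discharge (T1) largely repeats the admission (T0) window, so in-hospital falls are mixed with falls that precede the intervention

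*Protocol article*

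**What the plan says.** In the protocol article, Table 1 (under Secondary outcomes) gives one definition of fall frequency, "number of falls in the previous 6 months", and marks it in all four measurement columns. Severity is to be graded for each fall.

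The section Points of measurement places the four times "at admission to (T0) and discharge from hospital (T1) as well as 6 and 12 months after discharge". T0 and T1 are therefore the start and end of the same stay. The only information on its length is the patient inclusion criterion, which admits patients "who are likely to spend at least 5 days in the participating hospitals". No mean or maximum is given.

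The Objectives describe the intervention as a "pharmacist-based, patient-centered medication review prior to the patient’s discharge from hospital", so it takes place between T0 and T1. On analysis, Statistical methods says: "Secondary efficacy variables will be analyzed in an explorative way". The article gives no separate recall period for falls at T1.

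**The concern.** A six-month look-back suits three of the four times. At T0 it is a baseline. At T2 it runs from discharge to month 6, and at T3 from month 6 to month 12. At T1 it reaches back across the stay and then over most of the period already asked about at T0.

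Three things follow if the table is applied as printed:

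- A comparison of the arms at T1 rests mostly on falls that happened before the review could act.
- The stay has no clean count of its own. The T0 window ends at admission and the T2 window begins at discharge, so only T1 covers the stay.
- Severity is recorded again as well. A fall with injury that led to the index admission meets the table's definition of severe at T0 and, being still inside the window, again at T1.

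Other rows of Table 1 show that T1 was not marked by default. EQ-5D, TSQM, PEF-FB-9, IADL and re-hospitalization all omit it.

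**Working it through.** The article states no event rate, power or sample size for falls, so there is no figure of its own to reproduce. The check concerns the overlap of the windows.

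**Inputs**

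- Window W = 6 months = 365.25 / 2 = 182.6 days (Table 1).
- Stay L = time from T0 to T1. The article gives only a likely minimum of 5 days; 5 to 28 days is an assumed range.

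**Step 1: overlap in time.** With admission as day 0, the T0 window runs from −W to 0 and the T1 window from L − W to L. The share of the T1 window already covered at T0 is (W − L) / W, and the share that is the stay is L / W.

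| Stay L (days) | Already covered at T0 | Stay |
|---|---|---|
| 5 | 177.6 / 182.6 = 97.3% | 2.7% |
| 7 | 175.6 / 182.6 = 96.2% | 3.8% |
| 10 | 172.6 / 182.6 = 94.5% | 5.5% |
| 14 | 168.6 / 182.6 = 92.3% | 7.7% |
| 21 | 161.6 / 182.6 = 88.5% | 11.5% |
| 28 | 154.6 / 182.6 = 84.7% | 15.3% |

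**Step 2: from time to falls.** Shares of time equal shares of expected falls only if the fall rate is the same in and out of hospital. If the in-hospital rate were three times as high (assumed), the pre-admission share would be (W − L) / (W − L + 3L):

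- 5 days: 177.6 / 192.6 = 92.2%
- 14 days: 168.6 / 210.6 = 80.1%
- 28 days: 154.6 / 238.6 = 64.8%

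Pre-admission falls still form the majority.

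**Step 3: effect on a rate ratio.** Suppose, for illustration, that the review halved falls throughout the stay. The T1 rate ratio would be 1 − 0.5 × (share of expected falls that occur in the stay).

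| Stay (days) | Equal rates | Threefold in-hospital rate |
|---|---|---|
| 5 | 1 − 0.5 × 0.027 = 0.986 | 1 − 0.5 × 0.078 = 0.961 |
| 14 | 1 − 0.5 × 0.077 = 0.962 | 1 − 0.5 × 0.199 = 0.900 |
| 28 | 1 − 0.5 × 0.153 = 0.923 | 1 − 0.5 × 0.352 = 0.824 |

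A true in-hospital ratio of 0.5 would thus appear as a value between about 0.82 and 0.99.

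**Step 4: subtracting totals.** T1 − T0 = (falls from day 0 to L) − (falls from day −W to L − W). The second term is the set of falls that have dropped off the far end of the window. With equal rates the two terms have the same expectation, so the difference averages zero however many in-hospital falls there were. The totals alone do not return the in-hospital count; dated falls would.

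**Step 5: with the change.** If T1 counts falls since admission, its overlap with T0 is 0% and its window is the stay. If T1 is dropped for falls, the T0, T2 and T3 windows do not overlap.

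**The case against.** The strongest reply is that little depends on this. Falls are secondary and exploratory, the article does not name T1 as the comparison point for falls, and the windows that bear on a lasting effect are correctly placed. That stands, and it sets the weight of the point.

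Several stronger readings are tempting, but the document does not support them:

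- *The T1 count cannot reflect the stay or the intervention.* It can. The stay lies wholly inside the six months before discharge, so every in-hospital fall is counted. It is diluted, not excluded.
- *Any effect shrinks towards zero.* This is true of a ratio but not of an absolute difference. In comparable arms the pre-admission falls have the same expectation and cancel from the difference in mean counts, leaving extra noise. Adjustment for T0 would remove much of that noise; the article specifies such adjustment for the primary variables and does not say how falls are modelled.
- *Falls will be counted twice in the analysis.* No section sums the T0 and T1 counts or models them as repeated counts. The repeated recording is in the data collection; a double count would need an analysis that the article does not describe.
- *In-hospital falls cannot be identified.* Severity is graded fall by fall, so falls may be recorded individually, perhaps with dates. The form is not shown.

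It can also be said that Table 1 is a condensed overview and that the exact T1 question belongs to the full protocol or the form. This holds for what an article leaves out. Here, however, the article states a recall window and applies it to T1, and that statement does not fit. If the form already asks something else at T1, the table should say so.

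**Conclusion.** The point holds as a minor defect in a stated measurement definition. As printed, the T1 window repeats about 97% to 85% of its length from the period already covered at T0, for stays of 5 to 28 days. That range is an assumption, because the article gives only a likely minimum of 5 days. The percentages are shares of time and become shares of falls only under equal fall rates. With an assumed threefold in-hospital rate, the pre-admission share of falls is about 92% to 65%.

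The consequence is a T1 count that contains in-hospital falls but measures them poorly: noisier on the absolute scale, attenuated on the ratio scale, and not separable from totals unless falls are dated. The primary outcomes, the sample size and the falls comparisons at T2 and T3 are untouched.

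**What to change.** In Table 1 and on the T1 form, define falls at T1 as those since admission. Keep the six-month window at T0 as baseline and at T2 and T3. Because the T1 period would then differ in length between patients, the length of stay should be available as time at risk.

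The alternative is to remove the T1 mark for falls. That is simpler and leaves three windows that do not overlap, but falls during the stay would then not be captured.

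If the form already dates each fall, a note saying that T1 falls are restricted to the stay is enough.

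The cost is one table entry and one form question, with no added visit. The article reports that baseline data collection has begun and that randomization follows this six-month period, so the change could be made before the intervention period. T1 falls data already collected under the six-month wording should be marked as such.
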